### **10.3 RECORDING AEs AND SAEs**

Following notification of the occurrence of an AE or SAE, it is the responsibility of the relevant Site Leader to review all documentation and source data related to the incident, as well as recording and reporting the event to the relevant body/bodies (i.e. the PIs, HREC, and/or the TGA). The Site Leader must record all relevant information in the CRF and complete a SAE form, if the event meets the criteria of a 'serious' incident (as outlined in *Section 10.1*). Required information includes:

- Date of event onset
- Type of event
- Temporality
- Medication dosages
- The Site Leader's assessment of causality and severity
- Treatments/investigations required
- Time to resolution
- Incident outcome

These responsibilities may be delegated by a Site Leader to another suitably qualified medical doctor who is also a registered Investigator associated with the study (these responsibilities must be documented on the delegation log).

### **10.4 ASSESSMENT OF AEs AND SAEs**

A medically-qualified Investigator must assess all AEs/ADRs as they occur for their seriousness, expectedness, causality and severity. As this is a single arm study, all AEs will be assessed knowing that the participant is taking the IMP. Any event that is classified as 'Serious' (SAE/SADR/SUSAR) must be notified to the PIs within 24 hours of a Co-Investigator's first awareness of the event.

The Site Leaders will review all AEs that are reported by the Co-Investigators as ‘Serious’ at their respective hospital sites. A Site Leader may not downgrade an event that has been assessed by another Investigator as ‘serious’ (SAE, SADR or SUSAR), but they may upgrade a reported AE/ADR to a ‘serious event’ as they deem appropriate. A PI, Site Leader, or the Trial Manager must also organise to inform the Mercy Health *Human Research Ethics Committee* (HREC) of any new information or research that comes to light during the trial regarding the safety of the IMP which could impact on the ethical acceptability of the study’s continuation.

#### **10.4.1 Assessment of seriousness**

A medically-qualified Investigator who is named on the delegation log will make an assessment of any reported event’s seriousness (as defined in *Section 10.1*).

#### **10.4.2 Assessment of causality**

A medically-qualified Investigator will make an assessment of the likelihood of an AE/SAE being related to the IMP according to these definitions:

- ‘Unrelated’: Where an event is assessed as being not causally related to the administration of the IMP
- ‘Possibly related’: The AE is assessed as being possibly causally related to the IMP (based on the nature of the event, temporal relationship between AE and IMP dosing, concomitant medications, or the underlying medical condition). This assessment of causality will be referenced against the safety information detailed in the manufacturer’s Product Information (*Appendix 1*). The Investigator may further sub-classify this assessment as ‘unlikely, but possibly related’, or ‘likely to be related’, according to their assessment of the event

Note: If an AE is considered to be attributed to the interaction between the IMP and another concomitant medication - or where an AE could be linked to either the IMP or a concomitant medication - the AE must be categorised as an ADR of sulfasalazine.

#### **10.4.3 Assessment of expectedness**

If an event is classified as an ADR, the assessing Investigator must use the information in the manufacturer’s Product Information to assign a level of expectedness to the ADR, based on existing knowledge of the drug’s potential to cause that particular event. The ADR must be termed as either:

- ‘Expected’: The ADR is consistent with the known toxicity profile of the IMP, as outlined in the manufacturer’s Product Information (see *Appendix 1*); or
- ‘Unexpected’: The ADR is not consistent with the known toxicity profile of the IMP

#### 10.4.4 Assessment of severity

The assessing Investigator will assign one of the three following categories of severity for each AE/SAE, and record their findings on the CRF/AE form:

- ‘Mild’: An AE that is easily tolerated by the participant, causing minimal discomfort and does not interfere with normal, daily activities
- ‘Moderate’: An AE that causes sufficient discomfort and interferes with the participant’s normal, daily activities
- ‘Severe’: An AE that prevents the participants from being able to perform their normal daily activities

Note: ‘Severity’ and ‘seriousness’ should not be confused – a severity rating is used to describe the intensity of an event, while seriousness is a regulatory definition based on participant or event outcome (see *Section 10.1*). One AE might be serious but not severe (e.g. thrombocytopenia), while another could be severe but not serious (e.g. nausea).

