### 1.3 POTENTIAL RISKS TO PARTICIPANTS

We expect the proposed treatment will be safe and well tolerated. Sulfasalazine is classified as a 'category A' drug in pregnancy - it has historically been taken by large numbers of pregnant and child-bearing-aged women; and is not known to cause any increase in the frequency of direct harm, indirect harm, or anomalies in the developing fetus in either humans or animals (13). Importantly,

sulfasalazine therapy is currently continued as a treatment option for pregnant women who have concomitant rheumatoid arthritis or inflammatory bowel disease.

Possible fetal risks:

Not known to cause anomalies in/harm to the developing fetus (13).

Possible maternal risks:

Patients with preterm preeclampsia may experience discomforts or inconveniences relating to their admission to hospital, clinical examinations and blood tests, regardless of whether or not they decide to participate in the study. However, patients recruited to the study would undergo additional examinations and pathology tests that are supplementary to their routine clinical care, and as such, may experience an increase in these discomforts and inconveniences. These additional study requirements will be outlined in detail to all potential participants during the informed consent process.

Sulfasalazine is generally well-tolerated. Side effects relating to the medication can be either dose-related or idiosyncratic.

Dose-related side effects include gastrointestinal side effects (nausea, vomiting and diarrhoea), central nervous system (headache) and hematologic toxicities (including leukopenia, haemolytic anaemia and megaloblastic anaemia). Dose-related symptoms are generally experienced when taking sulfasalazine in larger doses (>4 grams per day) than we propose to administer in this study. Our participants will receive a maximum daily dose of 3 grams of sulfasalazine and will be monitored for dose-related side effects every 1-3 days by a member of the research team.

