#### Clinical endpoints/measures of interest:

- Adverse Events (AEs) in mother and/or baby
- Time (days) to delivery of pregnancy after initial sulfasalazine dose
- Change in maternal systolic and diastolic blood pressure (mmHg)
- Change in maternal proteinuria (g/mmol)
- Emergence of/change in other clinical symptoms of preeclampsia
- Maternal development of Haemolysis/Elevated Liver enzymes/Low Platelets (HELLP) syndrome
- Neonatal morbidity/mortality outcomes
- Acceptability of treatment and side effects to participants

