## 10.2 IDENTIFYING AEs AND SAEs

All AEs/SAEs will be recorded from the time a participant signs the consent form until their postnatal closing out visit or phone call has been completed. Worsening of preeclampsia disease indicators that follow the normal, expected clinical course of the disease will not be reported as an AE/SAE, but will be recorded in the CRF. Any AE must be recorded on the AE log page in the CRF. Antenatal admission to hospital will not be considered as an AE/SAE, as it follows the course of normal clinical management for this cohort. An escalation of hospitalisation (e.g. from general ward to intensive care) as a result of an ADR will be classified as a SAE/SADR.

Participants will be asked about the occurrence of AEs/SAEs at every research team contact episode during the study, using open-ended and non-leading questions (e.g. "Tell me about how you've been feeling"), as well as specific questions relating to any occurrence of common ADRs (e.g. gastrointestinal symptoms). Participants' medication charts will be reviewed to assess for study protocol compliance, as well as any major changes to concomitant medications. AEs/SAEs may also be identified via information from the medical history or other source documents (e.g. abnormal pathology test results not consistent with the woman's preeclampsia disease progression, such as aplastic anaemia). If there is any doubt whether or not an event or clinical observation constitutes an AE, the event will be recorded as an AE.

Known, common gastrointestinal side effects of sulfasalazine therapy (nausea, vomiting, diarrhoea) will be noted on the CRF but do not need to be recorded as AEs, unless meeting the criteria for a 'serious' or 'severe' event (see *Section 10.1*).

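### Section 10.4.4 grades every adverse event on tolerability, discomfort and daily activities, so a symptom-free laboratory abnormality can only be mild and an event in the baby fits no grade

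*Protocol*

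**What the plan says.** Protocol Section 10.4.4 sets the grading rule: "The assessing Investigator will assign one of the three following categories of severity for each AE/SAE". The three grades are:

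- Mild: "An AE that is easily tolerated by the participant, causing minimal discomfort and does not interfere with normal, daily activities".
- Moderate needs both discomfort and some disturbance of what the woman usually does.
- Severe: "An AE that prevents the participants from being able to perform their normal daily activities".

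A note in the same section separates severity from seriousness, and its example of an event that is one but not the other is a laboratory finding: "One AE might be serious but not severe (e.g. thrombocytopenia").

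Three other parts of the protocol decide which events reach this scale.

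- Section 10.2 lists among the sources of AEs "abnormal pathology test results not consistent with" the course of the woman's preeclampsia, with aplastic anaemia as the example.
- Section 1.3 names among the dose-related effects of sulfasalazine "hematologic toxicities (including leukopenia, haemolytic anaemia and megaloblastic anaemia"). The product information in Appendix 1 adds thrombocytopenia, agranulocytosis and pancytopenia under blood disorders, and raised liver enzymes under investigations.
- Section 2.2.2 lists as a clinical measure "Adverse Events (AEs) in mother and/or baby", and Section 3 says that the babies' records will be reviewed after birth for outcomes and AEs. Section 10.1, however, defines an AE as an occurrence in a study participant who was given the study drug.

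**The concern.** Safety is a primary objective (Section 2.1.1). With 20 women and no control arm, the safety evidence is a description of events. Severity is one of the few attributes attached to every event: Section 10.3 requires it on the record and Section 10.5 requires it in the first SAE report. If the scale cannot separate a slight laboratory change from a profound one, or has no criterion for a newborn, the grade tends to understate harm for laboratory events and is arbitrary or blank for babies. Those descriptions feed the six-monthly and final risk assessments in Section 12.4 and the case for a later randomised trial.

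This is a rule that the protocol states. It is not a detail left to an analysis plan. An SAP can say how grades are tabulated, but the investigator assigns the grade when the event is assessed.

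**Working it through.** No figure in the protocol rests on the severity scale, so there is no arithmetic to reproduce. The check sets each kind of event against each grade.

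| Grade | What it needs (10.4.4) | Maternal symptomatic event | Wholly symptom-free maternal laboratory abnormality | Event in the fetus or newborn |
|---|---|---|---|---|
| Mild | Easily tolerated, minimal discomfort, no interference | Can be applied | Met in full | No workable criterion |
| Moderate | Discomfort and interference | Can be applied | Neither element met | No workable criterion |
| Severe | Normal activities prevented | Can be applied | Not met | No workable criterion |
| Grades available | | 3 of 3 | 1 of 3 | 0 of 3 |

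**Laboratory events.**

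1. They are in scope. Section 10.2 treats abnormal results that preeclampsia does not explain as AEs.
2. A result that the woman cannot feel is easily tolerated, causes no discomfort and does not disturb her activities. It meets mild and fails the other two grades.
3. None of the three grades contains a numeric or organ-function element, so step 2 gives the same answer at any depth of abnormality.
4. The note in Section 10.4.4 agrees as far as it goes: it says that thrombocytopenia may be serious without being severe. It does not say mild. Mild is an inference from the three definitions, and it holds only when the event is wholly symptom-free.

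**Events in the baby.**

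1. Sections 2.2.2 and 3 both speak of AEs in the baby.
2. Each grade depends on the participant's tolerance, discomfort or daily activities. The protocol elsewhere distinguishes participants from their babies (for example in Section 2.1.1). Even if the baby is counted as a participant, a stillbirth or a newborn's respiratory disease gives the assessor nothing to apply.
3. Section 10.1 limits AEs to a participant given the study drug. Read narrowly, events in the baby are not AEs and need no grade, which contradicts Sections 2.2.2 and 3. Read broadly, they need a grade that does not exist. Either way the text needs repair.

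**Where the grade is used.** Section 6.3 refers to Section 10.4.4 and attaches a consequence to severe side effects. Section 10.2 uses severe, along with serious, to decide whether common gastrointestinal effects are recorded as AEs. A change to the scale therefore touches both places.

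**The case against.** The strongest reply is that severity is only a label and that the protocol protects the substance by other routes.

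- Seriousness is assessed separately (Section 10.1), with notification within 24 hours (Section 10.5), whatever the severity grade. Causality and expectedness are assessed separately too.
- Neonatal mortality and morbidity by organ system are outcomes in their own right in Sections 2.1.1 and 9.2.1, taken from the babies' records. They need no severity grade to be reported.
- Numeric blood count, liver and renal results are copied to the CRF (Section 7), so the depth of an abnormality is not lost.
- Worsening that follows the expected course of preeclampsia is not an AE (Section 10.2), which reduces the number of laboratory AEs that reach the scale.

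All of this stands, and it limits the point. It does not repair the grade itself, which must still be assigned to each event.

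A reader might also infer more than the documents support:

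- *That half of the primary safety outcome is lost.* One of the two safety items in Section 2.1.1 concerns the fetus or newborn, but it is captured as morbidity and mortality. Only the severity grade is missing.
- *That every laboratory toxicity of the drug will be graded mild.* This holds only for symptom-free abnormalities. Several conditions named in Section 1.3, such as rash, pancreatitis and pneumonitis, are not laboratory-only and can be graded on symptoms.
- *That grading rests on activities alone.* This is so for severe. Mild and moderate also use discomfort, and mild uses tolerability.
- *That a severity table in the primary result will mislead.* Section 9 promises no such table. The protocol requires only that the grade be recorded for each event.

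**Conclusion.** The point holds in limited form. The one severity scale in the protocol must be applied to every AE/SAE. It gives a symptom-free maternal laboratory abnormality only one possible grade, mild, and gives an event in the baby none. The AE definition in Section 10.1 also does not match the baby AEs in Sections 2.2.2 and 3.

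The number of events affected cannot be stated, because the protocol gives no rate for laboratory or neonatal AEs. The 20 expected babies are the most individuals for whom a grade could be unavailable, and only those who have an AE would count.

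The conclusion rests on two readings: that mild follows from the definitions for a wholly symptom-free event, and that no laboratory or neonatal scale is named elsewhere in this protocol. It is an inexpensive improvement to how harm is described. It does not show that the safety objective fails.

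**What to change.** 1. Keep the present scale in Section 10.4.4 for maternal symptomatic events.
2. Grade maternal laboratory AEs on a published numeric scale named in advance, using results already transcribed to the CRF.
3. Grade fetal and neonatal AEs on a separate scale named in advance, using the neonatal record review already planned.
4. Report the three groups separately.
5. Reconcile the AE definition in Section 10.1 with Sections 2.2.2 and 3, so that it is clear whether and how events in the baby are AEs. The SAE definition is built on the AE definition, so the same wording should settle both.
6. State how the uses of severe in Sections 6.3 and 10.2 relate to the revised grading. Any clinical threshold is for the investigators to decide.

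The cost is a change to the protocol and AE-form wording and slightly more grading work per event, with no new data collection. The chosen numeric scale must be read against pregnancy and preeclampsia baseline values. Otherwise changes due to the disease could be graded as toxicity.

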#### 10.5 REPORTING OF SAEs/SADRs/SUSARs

Once an investigator becomes aware that a study participant has experienced a SAE/SADR/SUSAR, the information will be immediately reported to the CPI (no later than 24 hours after the assessing Investigator’s first awareness of the event).

If an Investigator does not have detailed or complete information regarding the SAE/SADR/SUSAR, they should not delay informing the CPI about the event – once additional information is received, the SAE report form can be updated. The first submission of a SAE report form will outline an assessment of seriousness, causality, expectedness and severity (see *Sections 10.4.1- 10.4.4*) at the time of the initial report being made to the PIs.

SAE report forms can be submitted by hand to the co-ordinating trials office; transmitted by fax to **[contact]**; or sent in PDF format by email to [[contact]](mailto:[contact]) (Trial Manager); [[contact]](mailto:[contact]) (PI); and [[contact]](mailto:[contact]) (PI). If a report is being submitted outside of business hours, phone contact must also be made with the on-call PI. Where missing information is not subsequently sent through to the Trial Manager/PIs following an initial report, the relevant investigator will be contacted to follow up and obtain additional information. All SAE reports and follow up information will be retained and compiled by the relevant Site Leader (or designee) in the *Investigator Site File* (ISF).

The PIs and Trial Manager will organise onward reporting to HREC and/or the TGA (as appropriate) following any SAE/SADR/SUSAR experienced by a study participant during this trial, as outlined in Sections 10.6, 10.7 and Appendix 2.

## 10.6 REGULATORY REPORTING REQUIREMENTS

The following table (TABLE 3) and Appendix 2 from the TGA (19) summarises the reporting requirements for sponsors and clinical trial investigators relating to SAEs/SADRs/SUSARs in CTN/CTX scheme trials:

**TABLE 3: TGA reporting requirements summary for serious events in clinical trials under CTN/CTX schemes:**

Therapeutic Goods Administration

| Reporter                 | → Reports what?                               | → To whom?       | → In what format?             | → In what timeframe?                                                                                                                                                                                                                                                                                 |
|--------------------------|-----------------------------------------------|------------------|-------------------------------|------------------------------------------------------------------------------------------------------------------------------------------------------------------------------------------------------------------------------------------------------------------------------------------------------|
| Sponsor of trial         | Serious and unexpected adverse drug reactions | TGA*             | ADRAC blue card \$ | For fatal or life-threatening ADRs, send initial report within 7 calendar days of first knowledge. Follow up with complete report within 8 additional calendar days.

For all other serious and unexpected ADRs, full report no later than 15 calendar days of first knowledge by the sponsor. |
|                          | Other reactions and adverse events            | TGA              | Tabulation                    | On request by TGA.                                                                                                                                                                                                                                                                                   |
| Clinical investigator(s) | Adverse reactions/events                      | HREC             | As required by HREC           | As required by HREC                                                                                                                                                                                                                                                                                  |
|                          |                                               | Sponsor of trial | As per study protocol         | As per study protocol                                                                                                                                                                                                                                                                                |

\* Report should be clearly marked 'Clinical trial ADR' and sent to:

The Medical Adviser  
Experimental Drugs Section  
Drug Safety and Evaluation Branch  
Therapeutic Goods Administration  
[name]  
WODEN ACT 2606

\$ Or an appropriate format that contains the same information

As outlined in *Section 10.5*, Clinical Investigators must inform the PIs within 24 hours of their first knowledge of an AE that meet the criteria as being either ‘serious’ (as defined in *Sections 10.1 and 10.2*) and/or ‘unexpected’ (as outlined in *Sections 10.1 and 10.4.3*). The PIs and Trial Manager will initially inform HREC and the TGA of any SADRs/UADRs/SUSARs within 7 calendar days of their first knowledge of the event, with a full follow-up report due within 15 calendar days of their first knowledge of the event (as outlined in *TABLE 3*).

Other AEs/ADRs should be reported by the Co-Investigators in the CRF and forwarded to the PIs and Trial Manager in a timely manner. The PIs and Trial Manager will inform HREC of any events that meet the reporting requirements outlined by HREC in their conditional approval of the study.

## **10.7 FOLLOW UP PROCEDURES**

After recording an AE on the CRF (or recording and reporting a SAE), the event will be followed by the research team until a final outcome can be recorded. This may include follow up visits, assessments or other contact with the affected participant that are supplementary to the course of normal clinical care.

If a resolution to an event cannot be established by the Investigators, an explanation of the efforts made to do so will be recorded in the CRF or AE log; or as an addition to the SAE reporting form submitted to HREC and the PIs.

Follow-up information from any SAEs will be reported as updates to the initial report form and submitted by the PIs within regulatory timeframes to the TGA and/or the local HREC (as appropriate).

